### **6.3 Study procedures**

#### **Completeness of resection**

The primary outcome parameter completeness of the resection will be evaluated by transvaginal ultrasonography (TVU) (contrast sonography if inconclusive TVU) by an independent gynecologist or ultrasonographer blinded for the treatment arm or judgment of completeness by the surgeon who performed the hysteroscopic myomectomy. This TVU should be performed 6 weeks postoperatively in the follicular phase of the menstrual cycle.

### **Baseline characteristics**

At baseline the following characteristics are registered: body mass index, medical history, demographics, parity, age, smoking, type and number of myomas

### **Characteristics registered during the procedure**

- completeness of resection as judged by surgeon
- surgical complications
- anesthesiologic complications (desaturation, airway obstruction, dysrhythmias, blood pressure drops, ECG alterations)
- operating time
- intravasation/fluid deficit
- recovery time (time from end of procedure until completely awake and communicative)
- use of pain medication and dose
- pain intensity measured by VAS scores
- duration of hospitalization (hours)

### **Characteristics registered after the procedure**

Nausea and vomiting, sore throat, pain (VAS score)

### **Transvaginal Ultrasonography**

Participating women will have had a TVU at baseline when the diagnosis of submucous myomas is made and the size and type of myomas is described. Another TVU follows at 6 weeks after hysteroscopic myomectomy to assess the completeness of resection. This TVU is part of the current usual care, so no extra ultrasonography is needed for this study.

### **Questionnaires**

Participating women will fill in questionnaires at baseline, which will be given before the surgical procedure. During follow-up, patients will fill in questionnaires at 24 hours, 2 weeks, 8 weeks, 6 and 12 months after randomisation. Questionnaires will contain:

- Short questionnaire on side effects 24 hours after surgery.
- the EuroQoL (EQ-5D-5L) questionnaire (15 questions) to assess the quality of life
- PBAC scores to assess the amount of menstrual blood loss
- Uterine Fibroid Symptoms – Quality of Life (UFS-QoL) questionnaire (37 questions) to assess the quality of life focussing on patients suffering from uterine fibroids
- Recovery Index (RI-10) questionnaire (10 questions): to assess the patients' recovery process

- Medical Consumption Questionnaire (iMCQ)[32]: for cost effectiveness analysis
- Productivity Cost Questionnaire (iPCQ)[33] to assess productivity loss
- Short questionnaire on recurrence and re-interventions at 12 months after surgery.

|           | Side effects
Pain
(VAS) | EQ-5D-5L | PBAC | UFS-QoL | RI-10 | iMCQ | iPCQ | Re-intervention |
|-----------|-------------------------------|----------|------|---------|-------|------|------|-----------------|
| Baseline  |                               | X        | X    | X       |       |      |      |                 |
| 24 hours  | X                             | X        |      |         | X     |      |      |                 |
| 2 weeks   |                               | X        |      |         | X     |      |      |                 |
| 8 weeks   |                               | X        | X    | X       | X     | X    | X    |                 |
| 6 months  |                               |          |      |         |       | X    |      |                 |
| 12 months |                               | X        | X    | X       |       | X    |      | X               |

A patient preference study (for which a different study protocol will be created) will be conducted alongside the trial including evaluation of patient satisfaction.

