## SUMMARY

**Rationale:** Hysteroscopic myomectomies are performed in the majority of Dutch hospitals. The number of procedures for submucosal type 0 or I myomas between 1-3 cm performed in the operating room is estimated to be 3000 per year. Hysteroscopic myomectomy is currently performed in daycare under general anesthesia. A considerable cost reduction is expected when procedural sedation (PSA) is applied. The major contributing factors to the cost reduction are the shift from surgery in an operating theatre to an office-based setting, shorter hospital stay and outpatient care versus day care. We expect higher patient satisfaction, as hospital stay is shorter and side effects such as nausea are reduced. However, both safety and effectiveness – including the necessity for re-intervention due to incomplete resection – have not yet been fully evaluated.

**Objective:** Is hysteroscopic resection of submucous myomas under procedural sedation with propofol (PSA) in an outpatient setting a cost-effective alternative for hysteroscopic myomectomy performed under general anesthesia in the operation room?

**Study design:** non-inferiority, multicenter RCT, with a cost effectiveness analysis (CEA) alongside it.

**Study population:** patients with submucosal type 0 or I myomas (FIGO (PALM COEIN)) with a maximum diameter of 3 cm. We use a non-inferiority design: based on estimated risk of 2,5% incomplete resections in both groups, with an non-inferiority upper limit of 10%, 205 women are needed.

**Intervention:** hysteroscopic resection of submucous myomas under procedural sedation with propofol, compared to general anesthesia

**Main study parameters/endpoints:** 1) complete resection 2) costs, pain, menstrual blood loss (PBAC score), , quality of life, return to daily activities/work, hospitalization, (post)operative complications, re-interventions.

**Nature and extent of the burden and risks associated with participation, benefit and group relatedness:** Patients participating in this study are requested to complete a questionnaire at baseline, after 24 hours, 2 weeks, 8 weeks, 6 months and 12 months after the procedure. At 6 weeks after the procedure patients are asked to visit the outpatient department for a transvaginal ultrasound to assess the completeness of resection. This visit is part of the current usual care.

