**RELEVANCE FOR PRACTICE:** The Dutch Guideline 'Heavy menstrual bleeding' recommends hysteroscopic myomectomy as treatment of first choice in case of symptomatic submucous myomas. In the current situation, patients are admitted into daycare and they are operated under general anesthesia. Performing hysteroscopic myomectomy under propofol sedation will lead to numerous advantages. For the patients direct advantages are a shorter hospital stay, less risk related to general anesthesia, treatment in a patient friendly setting and adequate recovery to pre-procedural functional and physiological level. For the hospital organization it leads to less pressure on surgery waiting lists, more flexible scheduling and a cost-reduction. From a societal perspective a further cost reduction is expected because of faster return to normal activities and shorter absence of work.

**ANTICIPATED COST-EFFECTIVENESS:** With an incidence of 3000 myomas eligible to resect in an office setting annually, and an estimated cost saving of €595 per resection, an estimated cost reduction of almost 1,8 million euros can be expected from a healthcare perspective annually. When taking cost savings due to reduced productivity losses into account, the savings are around 2,8 million euros annually from a societal perspective. Not unimportant to add is that we expect this cost-reduction at a concurrent improvement in patient satisfaction and quality of life.

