### **9.2 Recruitment and consent**

The gynaecologist participating in the network will inform the patient about the study and refer the patients to dedicated research nurses. These nurses will counsel patients, ask for informed consent, and perform randomisation. The research nurse will organize the required treatments, depending on the result of the randomisation.

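### Section 6.3 times the follow-up questionnaires from randomisation, the Summary from the procedure; taken literally, 6.3 puts early recovery and quality-of-life forms before surgery

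*Protocol*

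**What the plan says.** The protocol gives two time origins for one questionnaire schedule.

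- Section 6.3, Questionnaires: "During follow-up, patients will fill in questionnaires at 24 hours, 2 weeks, 8 weeks, 6 and 12 months after randomisation".
- Summary, paragraph on burden and risks: "questionnaire at baseline, after 24 hours, 2 weeks, 8 weeks, 6 months and 12 months after the procedure".

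The list under the 6.3 sentence ties two of its own items to the operation: "Short questionnaire on side effects 24 hours after surgery" and "Short questionnaire on recurrence and re-interventions at 12 months after surgery". The schedule table that follows labels its rows by time only and names no origin. It places the RI-10 at 24 hours, 2 weeks and 8 weeks. The EQ-5D-5L is at baseline, those three times and 12 months. The PBAC and UFS-QoL are at baseline, 8 weeks and 12 months.

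On the order of events, section 9.2 has research nurses obtain consent and randomise, and then: "The research nurse will organize the required treatments, depending on the result of the randomisation". No minimum, maximum or expected interval from randomisation to surgery is given. The ultrasound for the primary outcome is timed six weeks postoperatively (sections 6.1.1 and 6.3).

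**The concern.** Randomisation and surgery are different days unless a woman is operated on at once, and the protocol plans surgery only after allocation. Section 6.3 is the operational text: section 6.2 has patients receive an e-mailed link, or paper forms by post, so whoever sets up that mailing needs one time zero. If the 6.3 sentence is followed, an instrument described as "Recovery Index (RI-10) questionnaire (10 questions): to assess the patients' recovery process" can be sent to women who have not yet had the operation.

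Quality of life and return to daily activities or work are named secondary objectives, and the EQ-5D-5L supplies the QALYs in section 8.2. A recovery form completed before surgery contains no recovery information, and no later analysis can replace it. The choice of clock therefore cannot be left to the analysis stage.

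**Working it through.** **The plan's own figure.** The only computed design figure is the sample size in section 4.4. Inputs: 2.5% incomplete resections in both arms, margin 7.5 points, one-sided alpha 0.025, power 90%, dropout 10%.

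n per arm = (1.960 + 1.282)² × 2 × 0.025 × 0.975 / 0.075² ≈ 91.1, rounded up to 92. Total 184; 184 / (1 − 0.10) = 204.4, rounded up to 205.

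This reproduces the stated 205. It concerns only the ultrasound outcome and does not depend on the questionnaire clock.

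**Questionnaire timing.** Inputs are the five scheduled times (1, 14, 56, about 182 and about 365 days) and the wait from randomisation to surgery. The protocol does not give the wait, so a range is assumed.

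Days since surgery = days since randomisation − wait in days.

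| Assumed wait | 24 h form | 2-week form | 8-week form | 6-month form | 12-month form |
|---|---|---|---|---|---|
| 1 week | −6 | +7 | +49 | +175 | +358 |
| 2 weeks | −13 | 0 | +42 | +168 | +351 |
| 4 weeks | −27 | −14 | +28 | +154 | +337 |
| 8 weeks | −55 | −42 | 0 | +126 | +309 |
| 12 weeks | −83 | −70 | −28 | +98 | +281 |

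Negative values are before surgery. Two thresholds follow without any assumed wait:

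- 1 − wait < 0 whenever the wait exceeds one day, so the 24-hour RI-10 and EQ-5D-5L are preoperative.
- 14 − wait < 0 whenever the wait exceeds 14 days, so the 2-week forms are preoperative.

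The RI-10 is collected at three times only. For a wait between 2 and 8 weeks, just its 8-week reading can be postoperative. This holds even if both arms wait equally.

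**Difference between arms.** Shift in postoperative time between arms = difference in waits. With assumed waits of 4 weeks (sedation) and 8 weeks (general anaesthesia), the 8-week form falls at +28 versus 0 days and the 12-month form at about +337 versus +309 days, a shift of 28 days throughout. With assumed waits of 3 and 6 weeks, the 8-week form falls at 8 − 3 = 5 versus 8 − 6 = 2 weeks after surgery. With equal waits the shift is zero.

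**With the procedure as origin.** The forms fall at 1, 14, 56, about 182 and about 365 days after surgery in both arms, whatever the wait.

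**The case against.** The strongest reply is that the intended clock is visible. The Summary counts from the procedure, two list items in 6.3 count from surgery, the ultrasound is postoperative, and a recovery index at 24 hours makes sense only after an operation. On this view the 6.3 wording is a drafting slip. That is probably right, but it does not remove the conflict: the sentence is current text, it is the one that sets the schedule, and the table does not settle which origin applies.

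Three stronger readings are tempting, and the protocol does not support them.

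- A reader might infer that every follow-up form is affected, including 24-hour side effects and pain. The side-effect form is expressly set at 24 hours after surgery, and pain shares its table column; the re-intervention form is also tied to surgery.
- A reader might infer that the protocol expects women in the general anaesthesia arm to wait longer. The introduction says that sedation brings the hospital "less pressure on surgery waiting lists, more flexible scheduling and a cost-reduction". That describes an organisational effect of adopting sedation, not waits by arm in this trial. Unequal waits are a reasonable inference, no more.
- A reader might infer a systematic bias between arms. That needs both literal use of the 6.3 sentence and unequal waits; the protocol gives no waits.

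It can also be said that a randomisation clock is legitimate for 12-month costs and QALYs in an intention-to-treat economic evaluation, and that a pure procedure clock leaves a woman who is never operated on without a time zero. Both points stand and are taken into the fix.

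**Conclusion.** The point holds as a contradiction in current text that makes the 6.3 schedule wrong as written. Followed literally, it makes the 24-hour RI-10 and EQ-5D-5L preoperative for any wait over one day and the 2-week forms preoperative for any wait over two weeks. These thresholds rest only on the stated times and on surgery following randomisation.

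Beyond that, the RI-10, EQ-5D-5L, PBAC and UFS-QoL would be taken at postoperative times that vary from woman to woman. They would differ by arm only if waits differ, and the size of that difference cannot be derived from the protocol; the waits used above are illustrations.

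The consequence is confined to questionnaire-based secondary and cost-utility outcomes. The side-effect and pain form, the re-intervention form, the primary ultrasound outcome, the margin and the sample size are untouched. Correction is still warranted before data collection, because early recovery data missed in this way cannot be restored.

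**What to change.** - In section 6.3, count the follow-up questionnaires from the procedure instead of randomisation, in line with the Summary and the two surgery-based list items. Add the same origin to the schedule table.
- Trigger the e-mailed links and postal forms from the recorded procedure date.
- Record the interval from randomisation to procedure and report it by arm.
- State a time zero for women who are randomised but not operated on.
- If a randomisation clock is wanted for 12-month costs and QALYs, say so separately in section 8.2. That section also lists cost questionnaires at 6 weeks, 3, 6 and 12 months, whereas the 6.3 table has the iMCQ at 8 weeks, 6 and 12 months; the change of origin does not resolve this, so the two should be reconciled at the same time.

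The cost is a short protocol amendment, a trigger date in the web database and one recorded interval per woman. The sample size stays at 205.

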#### 6.4 Withdrawal of individual subjects

Subjects can leave the study at any time for any reason if they wish to do so without any consequences. The investigator can decide to withdraw a subject from the study for urgent medical reasons.

## **7. SAFETY REPORTING**

### **7.1 Section 10 WMO event**

In accordance to section 10, subsection 1, of the WMO, the investigator will inform the subjects and the reviewing accredited METC if anything occurs, on the basis of which it appears that the disadvantages of participation may be significantly greater than was foreseen in the research proposal. The study will be suspended pending further review by the accredited METC, except insofar as suspension would jeopardise the subjects' health. The investigator will take care that all subjects are kept informed.

### **7.2 AEs, SAEs**

#### **7.2.1 Adverse events (AEs)**

Adverse events are defined as any undesirable experience occurring to a subject during the study, whether or not considered related to [the investigational product / the experimental intervention]. All adverse events reported spontaneously by the subject or observed by the investigator or his staff will be recorded.

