#### **6.1.2 Secondary study parameters/endpoints**

Secondary outcomes are cost effectiveness, pain, menstrual blood loss (PBAC score), quality of life, return to daily activities/work, hospitalization, (post)operative complications, re-interventions. These secondary parameters will be assessed by several questionnaires.

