### **7.3 Follow-up of adverse events**

All AEs will be followed until they have abated, or until a stable situation has been reached. Depending on the event, follow up may require additional tests or medical procedures as indicated, and/or referral to the general physician or a medical specialist. SAEs need to be reported till end of study within the Netherlands, as defined in the protocol

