### **10.4 End of study report**

The investigator will notify the accredited METC of the end of the study within a period of 8 weeks. The end of the study is defined as the last patient's last visit.

In case the study is ended prematurely, the investigator will notify the accredited METC within 15 days, including the reasons for the premature termination.

Within one year after the end of the study, the investigator/sponsor will submit a final study report with the results of the study, including any publications/abstracts of the study,

to the accredited METC.

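### Complications after 24 hours have no scheduled question although questionnaires are named as their source, re-interventions are asked about directly only once, and the end-of-study definition may cut SAE reporting short for late enrolees

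*Protocol*

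**What the plan says.** Section 6.1.2 of the protocol includes "return to daily activities/work, hospitalization, (post)operative complications, re-interventions" among the secondary outcomes and then gives their source: "These secondary parameters will be assessed by several questionnaires".

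Section 6.3 lists the questionnaires. Two concern these outcomes by name: "Short questionnaire on side effects 24 hours after surgery" and "Short questionnaire on recurrence and re-interventions at 12 months after surgery". The schedule table marks the first only in the 24-hour row and the second only in the 12-month row. The iMCQ, on health-care use, is marked at 8 weeks, 6 months and 12 months; its stated purpose is "for cost effectiveness analysis".

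Section 6.3 also has fixed registration lists. The list for the procedure includes surgical and anesthesiologic complications. The list for afterwards holds nausea or vomiting, sore throat and pain. The 6-week visit is described only as an ultrasound to judge completeness of resection.

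For everything else, section 7.2.1 applies: "All adverse events reported spontaneously by the subject or observed by the investigator or his staff will be recorded". Section 8.1 sends complications and re-interventions to an independent Clinical Evaluation Committee, blinded where possible.

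On the reporting window, section 7.3 says: "SAEs need to be reported till end of study within the Netherlands, as defined in the protocol". Section 10.4 says: "The end of the study is defined as the last patient's last visit". Section 3 plans 12 months of follow-up and names complications as part of it.

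**The concern.** A named secondary safety outcome does not have the instrument that section 6.1.2 says it has. A complication that arises after the first day, such as an infection or late bleeding, is recorded only if the woman mentions it or staff happen to see it. Section 6.2 states that patients and care staff cannot be blinded, so the readiness to report or record may depend on the arm. The committee in section 8.1 classifies the events it receives. Nothing says that it looks for them, so blinding the committee cannot repair unequal detection upstream.

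This matters because the Summary and section 1 give safety, and re-intervention after incomplete resection, as what has not yet been fully evaluated. It is also not a detail that an analysis plan could settle, since no analysis recovers events that nobody asked about.

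The end-of-study wording raises a second question: whether women enrolled late are covered for SAEs over the 12 months that section 3 foresees.

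**Working it through.** The plan attaches no figure to this point, so the first two steps compare sections and the third is a short calculation.

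**1. What is asked about complications, and when (section 6.3)**

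| Time | Scheduled collection | Complication item described? |
|---|---|---|
| Procedure | Fixed list with surgical and anesthesiologic complications | Yes |
| Shortly after | Nausea/vomiting, sore throat, pain | Early side effects only |
| 24 hours | Side effects/pain, EQ-5D-5L, RI-10 | Early side effects only |
| 2 weeks | EQ-5D-5L, RI-10 | No |
| 6 weeks | Visit with transvaginal ultrasound | No |
| 8 weeks | EQ-5D-5L, PBAC, UFS-QoL, RI-10, iMCQ, iPCQ | No |
| 6 months | iMCQ | No |
| 12 months | EQ-5D-5L, PBAC, UFS-QoL, iMCQ, re-interventions | No |

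After 24 hours the last column is empty of complication items. For that period section 6.1.2 and section 6.3 do not agree, and the rule in section 7.2.1 is all that remains for non-serious events.

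**2. Re-interventions**

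There is one direct question, at 12 months, the same in both arms. The iMCQ may show indirectly that care was used, but the protocol does not link it to re-interventions or to the committee. No check against hospital records is described, so a woman who does not return the 12-month form may be lost for this outcome.

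**3. SAE reporting window**

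Inputs: 24 months of inclusion and 12 months of follow-up (section 3); one visit scheduled after surgery, at 6 weeks (Summary, section 6.3); end of study at the last patient's last visit (section 10.4). For simplicity, assume that the last woman is treated at month 24. Let t be the month in which a given woman is treated. Six weeks is 6/52 × 12 = 1.38 months.

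- Reading A, the last visit is the 6-week ultrasound: coverage = (24 − t) + 1.38 months.
  - First woman (t = 0): 25.4 months.
  - Last woman (t = 24): 1.4 months, i.e. 6 weeks.
  - Coverage is below 12 months when t > 24 + 1.38 − 12 = 13.4, i.e. in the last 24 − 13.4 = 10.6 months of inclusion. If recruitment were even (an assumption), that is 10.6/24 = 44% of the women.
- Reading B, the last visit is the 12-month contact: coverage = (24 − t) + 12 months, so at least 12 months for everyone.

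The protocol does not say which reading is meant. The word visit favours A, because the later contacts are questionnaires completed online or by post (section 6.2). The 12-month follow-up in section 3 favours B.

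**The case against.** Much collection is already systematic. Surgical and anesthesiologic complications are on a fixed list, early side effects are registered, re-interventions have a scheduled question in both arms, and the iMCQ gives indirect information at three times. A reader might infer that these outcomes have no systematic source at all; the documents contradict that.

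Section 7.2.1 also covers events that staff observe, and all women are asked to come at 6 weeks, where a clinician may well ask. The case report form, which is not available here, may contain such items. That is possible, but it does not resolve the mismatch between sections 6.1.2 and 6.3, and the protocol gives that visit no such task.

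The case for a difference between arms has limits. The care settings differ mainly on the day of the procedure, when registration is fixed. Afterwards both arms have the same visit and the same forms. What stands is the ordinary risk of unprompted reporting without blinding: undercounting is plausible, and imbalance is possible but not shown.

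A reader might also infer that SAE reporting stops for each woman at her own 6-week visit. It does not: the end of study is one date for the whole trial, and only late enrolees can fall short, under reading A.

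Finally, it is tempting to state how many events would be missed, by applying the 3.2% complication risk in section 1, the 10% drop-out or the 2.5% incomplete resections in section 4.4 to 205 women. The documents do not support this. They give no timing of complications, no non-response rate at 12 months, and no conversion from incomplete resection to re-intervention.

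**Conclusion.** The point holds in limited form. Section 6.1.2 promises collection by questionnaire that section 6.3 does not provide for complications after 24 hours, and re-interventions rest on a single direct question at 12 months. Followed as written, the plan is likely to under-collect a named secondary safety outcome, possibly unequally between arms. The size cannot be given from the documents.

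The SAE window is an ambiguity, not an established gap. Under reading A, women treated in about the last 10.6 months of inclusion have less than 12 months of reporting, down to 6 weeks for the last one. Under reading B there is no shortfall.

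None of this touches the primary endpoint, which has its own scheduled, blinded assessment. The changes are worth making because safety is part of the trial's stated rationale and they use contacts that already exist.

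**What to change.** 1. At the existing 6-week visit, complete a short fixed checklist of complications since discharge, identical in both arms. Add the same items to the 2-week and 8-week questionnaires, and align sections 6.1.2 and 6.3.
2. At 12 months, have the research nurses already working in the centres confirm re-interventions and readmissions from the treating hospital's record, within the consent given. Keep the questionnaire to pick up care received elsewhere, and send both to the Clinical Evaluation Committee. For women who withdraw, the consent decides whether the record may be used.
3. In section 10.4, define the end of study as the last patient's 12-month follow-up contact, so that section 7.3 covers 12 months for every woman.

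The cost is a one-page checklist, a few questionnaire items, a record check for each woman and some protocol wording. The drawbacks are slightly more data entry and more minor events recorded. The consent text should be checked for the record look-up before it is adopted.
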